### Criteria for discontinuing or modifying allocated interventions {11b}

Patients can leave the study at any time for any reason if they wish to do so without any consequences. The patient’s participation in this study can also be ended by the investigator if the patient is uncooperative and/or does not attend study visits. The patient data that have been collected up to that moment will be included in the analysis. In case too many data are missing, the patient will be replaced by a new patient. If there are adverse events or postoperative complications, the study will be terminated early. In case of illness, patients will be asked to contact the primary investigator. Patients that are discovered after surgery not to meet the criteria will not receive acupuncture treatment and will be treated according to the standard of care. These patients will be removed from the study. Patient data included up to that moment will be included in the analysis.

Criteria for study termination include the following: ① The pain of acupuncture was intolerable or serious adverse reactions occurred; ② during the treatment, the symptoms worsened or other critical diseases appeared, and the patients could not continue the treatment; ③ researchers found that there were serious safety problems; ④ because of various reasons cannot adhere to the treatment.

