#### Secondary outcomes

Secondary outcomes include the time of first postoperative defecation, time of first fluid intake, and time of first ambulation, which are obtained through the assistance of family members and caregivers, via inquiry and records of patient’s status. Other secondary outcome measures such as gastrointestinal reaction score (postoperative pains, distention, nausea, vomiting), acupuncture sensation evaluation scale, laboratory test, postoperative hospital stay, quality of life, readmission rate, and other postoperative complications (fever, pneumonia, wound infection, bleeding, etc.) are assessed and evaluated by our investigators. The first postoperative evaluation of all patients was performed 12–24 h after operation to ensure that the patients were awake.

For gastrointestinal reaction score, postoperative pain will be evaluated regularly at three times a day using the visual analog scale (VAS), and the three scores will be averaged and tabulated with dosage and frequency of patient-controlled analgesia (PCA) and analgesic medication used. The extent of distention is recorded using the Likert scale [17], postoperatively from day 1 to 4. The extent of nausea is recorded using the VAS, postoperative from day 1 to 4. Vomiting will be counted daily.

For Acupuncture Sensation Evaluation Scale, acupuncture sensations are assessed after every acupuncture treatment session through inquiring about patient’s sensations.

For laboratory test, venous blood will also be collected on the day prior to operation, as well as the first and third day after the laparoscopy, to assess the safety of acupuncture base on blood examinations and biochemical indicators.

Postoperative hospital stay is measured from the day of the laparoscopy procedure till the day of discharge.

Quality of life is assessed through the Quality of Life Questionnaire (QLQ-c30), provided to patients prior to operation and 1 month after the operation [18].

For readmission rate, evaluate the readmission of patients 1 month after the operation, record the reasons for readmission in detail, and finally calculate and analyze.

Adverse events include postoperative complications and adverse acupuncture events. Postoperative complications are recorded and evaluated using the Clavien Dindo Classification [19]. Adverse acupuncture events including subcutaneous hematoma, continuous acupuncture afterfeeling, and needle stagnation will be recorded by the assessor.

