### Statistical methods

#### Statistical methods for primary and secondary outcomes {20a}

Spss22.0 software was used to analyze and process the clinical observation data, in which in the descriptive statistical analysis, qualitative indicators were described by frequency table and percentage and quantitative indicators were described by mean and standard deviation. Comparison of the two groups was performed: quantitative data in line with normal distribution using the *t* test, homogeneity test of variance between groups, with 0.05 as the test level, uneven variance using Satterthwaite method for correction of *t* test, and not in line with normal distribution using Wilcoxon rank-sum test. The hypothesis test uses a two-sided test and gives the test statistics and the corresponding *p* value, with *p* ≤ 0.05 as statistically significant. All (S)AE(I)s will be summarized and recorded including the nature, date and time of onset, date of resolution, determination of seriousness, severity, action taken, outcome, and possible causality to study treatment. SAE data will be presented in a descriptive manner.

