#### Methods in analysis to handle protocol non-adherence and any statistical methods to handle missing data {20c}

The primary outcome will be assessed using an intention-to-treat analysis. Missing data will be reduced to a minimum by using the appropriate measures described above. Mixed models do not require imputations for missing data. If any statistical method is needed to account for missing data in the secondary outcomes, multiple imputation will be used.

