#### Adverse event reporting and harms {22}

All adverse events reported by the subject or observed by the investigators will be recorded. The causality to the study treatment event will be recorded. Some complications are considered as adverse events of special interest (AESI): such as fever, bleeding, wound infection, intestinal obstruction, gastroenteric paralysis, anastomotic leakage, pneumonia, deep vein thrombosis, etc. Serious adverse events (SAEs) should be reported to the ethics committee of Dong Fang Hospital in time.

Safety evaluation of acupuncture: needle breaking, needle leaving, needle fainting, local hematoma, infection, and abscess; incidence and average times of other discomfort after acupuncture (pain, nausea, vomiting, palpitation, dizziness, headache, anorexia, and insomnia). Form a specific record form, and ask whether the above situation occurs during the diagnosis and treatment of each patient. If so, record it immediately.

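### Multiple imputation is the only method named for missing secondary outcomes, with no separation of a first event not yet seen from a time that was simply not recorded

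*Protocol article*

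**What the plan says.** The section on non-adherence and missing data {20c} gives one rule for this family of outcomes: "If any statistical method is needed to account for missing data in the secondary outcomes, multiple imputation will be used". It attaches no imputation model and no exception.

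The outcomes section lists times to a first event among them: "Secondary outcomes include the time of first postoperative defecation, time of first fluid intake, and time of first ambulation". These times are gathered by asking relatives and carers and from notes on the patient's condition, and no end of observation is given for them. Length of stay is a separate secondary outcome: "Postoperative hospital stay is measured from the day of the laparoscopy procedure till the day of discharge".

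The statistical methods section {20a} summarises quantitative outcomes by mean and standard deviation and compares them in two ways: "quantitative data in line with normal distribution using the *t* test", and data "not in line with normal distribution using Wilcoxon rank-sum test". It names no method for censored times.

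The protocol foresees patients who may not reach the event while observed. The stopping criteria {11b} include the case where "during the treatment, the symptoms worsened or other critical diseases appeared, and the patients could not continue the treatment". The adverse events of special interest {22} are complications "such as fever, bleeding, wound infection, intestinal obstruction, gastroenteric paralysis, anastomotic leakage, pneumonia".

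**The concern.** A first-defecation time can be absent for two different reasons. Either the event happened and nobody noted when, or it had not happened when the patient was last asked. The first is missing data, and multiple imputation is a reasonable answer. The second is right-censoring: the time is unknown but has a known lower bound.

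Ordinary multiple imputation treats both alike. It fits a model to the patients with a recorded time, who are on average the faster ones, and draws from it. A drawn time can fall before a moment at which the patient was known not to have had the event. A patient with a paralysed bowel can then be scored as a typical recovery, in a trial whose subject is delayed bowel recovery. If the arms differ in how many such patients they have, the comparison is distorted.

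The point concerns secondary outcomes, chiefly first defecation. It does not touch the primary outcome.

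**Working it through.** **No figure to reproduce.** The protocol gives no expected defecation time, discharge time or number of patients without the event. Every input below is an assumption.

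**Assumed inputs.** First defecation T: mean 72 h (60 h in an arm that truly recovers 12 h faster), SD 24 h. End of observation D: here discharge, mean 120 to 144 h, SD 30 h. Correlation of T and D: 0 or 0.6. 80 per arm. T is unobserved if T > D. That recording ends at discharge is itself an assumption, used only to generate unobserved events.

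**Step 1: share unobserved.** With s = √(SD_T² + SD_D² − 2·corr·SD_T·SD_D) and z = (mean D − mean T)/s, the share is Φ(−z). At correlation 0, s = √(576 + 900) = 38.42 h.

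- D = 120 h: z = 48/38.42 = 1.249, share 10.6%
- D = 132 h: z = 60/38.42 = 1.562, share 5.9%
- D = 144 h: z = 72/38.42 = 1.874, share 3.0%

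**Step 2: error in one arm's mean.** Within-arm imputation without covariates reproduces, on average, the mean of the observed times. That mean is too early by [(SD_T² − corr·SD_T·SD_D)/s] × φ(z)/Φ(z). At correlation 0 the first factor is 576/38.42 = 14.99.

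- D = 120 h: 14.99 × 0.1828/0.8942 = 3.06 h
- D = 132 h: 14.99 × 0.1178/0.9408 = 1.88 h
- D = 144 h: 14.99 × 0.0689/0.9695 = 1.07 h

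**Step 3: error in the difference.** This is the gap between the two arm errors. Acupuncture at 120 h against control at 144 h with no true effect gives −(3.06 − 1.07) = −1.99 h. At correlation 0.6, s = √(1476 − 864) = 24.74 h and the first factor is 144/24.74 = 5.82. The arm errors are 0.36 h and 0.03 h, a difference of −0.33 h.

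**Step 4: simulation.** 1,500 trials per scenario, 10 normal-model imputations within arm, without and with discharge time as a predictor. Estimates are acupuncture minus control, and negative favours acupuncture.

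| Scenario | Unobserved, acupuncture v control | True difference | Imputed difference |
|---|---|---|---|
| Discharged 24 h sooner | 11% v 3% | 0 | −2.1 to −2.5 h |
| Discharged 12 h sooner | 6% v 3% | 0 | −0.8 to −1.0 h |
| Discharged 24 h sooner, correlation 0.6 | 3% v 0% | 0 | −0.3 to −0.9 h |
| Equal discharge | 6% v 6% | 0 | about 0 |
| Recovers 12 h faster, discharged 12 h sooner | 6% v 6% | −12 h | −12.0 to −12.1 h |
| Recovers 12 h faster, equal discharge | 3% v 6% | −12 h | −11.0 to −11.3 h |

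The simulation agrees with the closed form. In the equal-discharge row each arm's mean is still about 2 h too early; the two errors cancel.

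**Step 5: bowel failure.** Suppose a failed patient's time is truly late, assumed 168 h, and imputation assigns 72 h on average. The error per failed patient is 168 − 72 = 96 h. With 5% failures in one arm and 10% in the other, imputation hides 0.05 × 96 = 4.8 h. With 2% and 10% it hides 0.08 × 96 = 7.7 h. Both errors favour the arm with more failures.

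**The case against.** The strongest reply is that the rule is conditional and names no model. It applies only if a method is needed, and imputation restricted to times after the last event-free moment is still multiple imputation. Such detail is often left to an analysis plan, which is not shown. This limits the point but does not remove it. When a method is needed, this is the one fixed, and neither it nor the t test and rank-sum test recognise an event not yet seen. A plan that follows the text as written would inherit the problem.

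A reader might infer that imputation favours the arm sent home sooner. The protocol does not support that. It nowhere says recording stops at discharge: times come from family and caregivers by inquiry, and patients are contacted again at 1 month. The table also shows that the error disappears when discharge and bowel recovery move together, and works against acupuncture when only recovery improves.

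A reader might also infer a badly inflated error rate. Two-sided false-positive rates of 18 to 23% can be produced, but only with a 24 h discharge gap and no bowel benefit, discharge independent of bowel recovery, and up to 36% of acupuncture patients without a time. They also rest on a test of means in skewed data, which the protocol would send to the rank-sum test. Nothing in the protocol supports those inputs.

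Two further limits stand. Early feeding and ambulation are part of care in both arms, so fluid intake and ambulation will seldom be unobserved. Some failures also drop out earlier: the exclusions cover colostomy and complications needing intensive care, and {11b} lets a patient with too much missing data be replaced. That replacement rule is no comfort, since it could remove the very patients at issue before any imputation.

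**Conclusion.** The point holds in a limited form. The protocol fixes one method for missing secondary outcomes without separating an event not yet seen from a value not recorded. For first defecation, ordinary imputation then discards a known lower bound and makes each arm's mean too early.

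The between-arm error follows the arms' shares of unobserved events. It favours the arm with the larger share and is near zero when the shares match. Its size is roughly 0.3 to 2.5 h with up to 3 to 11% unobserved in the worse-affected arm. It is larger if many more times are unobserved or, as in Step 5, if the unobserved times are very late. All of these sizes rest on assumed means, SDs, discharge times and failure rates. No fixed direction and no particular false-positive rate can be claimed. The change should be made, as a correction to a secondary analysis.

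**What to change.** In {20c}, split the rule in two.

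- **Values not recorded.** Keep multiple imputation for QLQ-C30, the symptom scores, and event times where the event is known to have happened but its time was not noted.
- **Events not yet seen.** For first defecation, and for fluid intake or ambulation if the case arises, treat the patient as right-censored at the last event-free inquiry and compare arms by log-rank test or Cox model. A patient whose bowel failed, or who had a reoperation or stoma before the event, should not be censored at that point as if non-informative. Keep that patient in the risk set as not recovered. Alternatively, rank such patients last in the rank-sum test already named in {20a}.

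Record the last event-free inquiry, and ask the date of first defecation at the planned 1-month contact so that few times stay unobserved.

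The cost is a few sentences and one question at an existing contact. Results for these outcomes become medians or hazard ratios in place of mean hours, and a date recalled after a month is imprecise. Censoring at withdrawal still assumes that leaving is unrelated to bowel recovery, so reasons for withdrawal should be reported by arm.

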#### Plans to give access to the full protocol, participant-level data, and statistical code {31c}

The datasets used and/or analysed during the current study can be made available by the corresponding author upon reasonable request and in agreement with the research collaboration and data transfer guidelines of the Dong Fang Hospital, Beijing University of Chinese Medicine.

### Oversight and monitoring

#### Composition of the coordinating center and trial steering committee {5d}

This is a single-center study designed in Dong Fang Hospital of Beijing University of traditional Chinese medicine and implemented and coordinated in Cancer Hospital of Chinese Academy of Medical Sciences.

Daily support for the trial was provided by:

Main responsible person: responsible for supervising the trial and the medical responsibility of patients.

Data manager: organize data capture and protect quality and data.

Study coordinator: trial registration, informing patients, coordinating study visits, and annual safety report.

Research surgeons: recruit patients, evaluate their postoperative recovery, and ensure follow-up in accordance with the agreement.

The study team meets biweekly. There is no trial steering committee or stakeholder and public involvement group.

#### Composition of the data monitoring committee, its role, and reporting structure {21a}

No data security monitoring board (DSMB) was designated in this study. The decision was based on the absence of serious adverse events in the pre-trial. In addition, since this is not a double-blind trial, there is no need for DMSB to protect researchers and doctors from blindness. A colorectal cancer surgeon will be designated as the safety officer for this study. In case of serious adverse events, the safety officer will be contacted within 48 h. The safety officer will assess whether the serious adverse event is (definitely or possibly) related to the treatment. If there is a (possible) handling relationship, further safety measures will be taken based on the advice of the safety officer.

#### Adverse event reporting and harms {22}

All adverse events reported by the subject or observed by the investigators will be recorded. The causality to the study treatment event will be recorded. Some complications are considered as adverse events of special interest (AESI): such as fever, bleeding, wound infection, intestinal obstruction, gastroenteric paralysis, anastomotic leakage, pneumonia, deep vein thrombosis, etc. Serious adverse events (SAEs) should be reported to the ethics committee of Dong Fang Hospital in time.

Safety evaluation of acupuncture: needle breaking, needle leaving, needle fainting, local hematoma, infection, and abscess; incidence and average times of other discomfort after acupuncture (pain, nausea, vomiting, palpitation, dizziness, headache, anorexia, and insomnia). Form a specific record form, and ask whether the above situation occurs during the diagnosis and treatment of each patient. If so, record it immediately.

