## Introduction

### Background and rationale {6a}

Colorectal cancer is a common malignant condition involving the gastrointestinal tract. With the aging population and changes in diet structures, incidence and mortality rates of colorectal cancer have seen a rising trend through the years [1]. Epidemiological studies have shown [2, 3] that in 2016, newly diagnosed cases and deaths of colorectal cancer in the USA were 135,000 and 50,000, respectively, and China has a higher ratio of newly diagnosed cases to death (50.8%) when compared with the USA (37%). In China, the incidence of colorectal cancer in males and females ranked 4th and 3rd, respectively, while mortality rates ranked 5th and 4th, respectively. The incidence of colorectal cancer for the age group below 50 has also shown an increasing trend. Surgical intervention remains the main treatment for colorectal cancer, despite surgical trauma and postoperative complications. Postoperative gastrointestinal dysfunction (PGID) is one of the most common complications and is often associated with administration of anesthesia, surgical retraction, postoperative fasting, usage of analgesics, prolonged bed rest, etc. [4, 5], and include symptoms such as distention and absence of flatus or bowel, accompanied by varying degrees of nausea, vomiting, and fever, leading to longer recovery periods, decrease in quality of life, and increase consumption of medical resources [6]. Current methods to promote recovery of gastrointestinal function include postoperative conventional treatments and prokinetic drugs such as domperidone and cisapride. However, the therapeutic efficacy of these drugs is less than ideal and accompanied with various side effects, possibly due to over-stimulation of gastrointestinal motility that could affect postoperative recovery negatively [7].

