### Acupuncture group

Patients in AG will receive acupuncture treatment in addition to perioperative care guided by ERAS protocols. Acupuncture treatment will be performed once daily, consecutively over 4 days, starting on the first day after the laparoscopy. Patients will assume a supine position for the treatment. Treatment will be carried out by a licensed acupuncturist who holds a China Acupuncturist Certification, with at least 2 years of clinical experience in acupuncture. The site of insertions will be swabbed and disinfected with 75% alcohol prior to needle insertion. Sterile, single-use acupuncture needles with diameter 0.30 mm and length 40 mm (China Suzhou, Huatuo) are used. Acupuncture points are selected based on Traditional Chinese Medicine (TCM) theory and clinical experience: ST36 Zusanli, ST37 Shangjuxu, PC6 Neiguan, LI4 Hegu (Fig. 2). Exact locations and depth of insertions are referenced from the 2006 National Standards of the People’s Republic of China (GB/T12346-2006) “Nomenclature and Location of Acupuncture Points” [16] (Table 2). After insertion of needles, stimulation of acupoints will be performed every 10 min, and each operation lasts at least 10 s, through lifting-thrusting and twirling-twisting manipulations, to achieve sensations of *deqi*. Needles are kept inserted for 30min.

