### Control group

Patients in CG will only receive ERAS care with no acupuncture intervention.

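### General discomforts after needling are measured as acupuncture safety with no between-arm comparison defined, although several are background postoperative symptoms; ask about them identically in both arms and report by arm

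*Protocol article*

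**What the plan says.** All references are to the protocol article.

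- **Adverse event reporting and harms {22}.** Besides needle-specific events, the safety evaluation of acupuncture covers the "incidence and average times of other discomfort after acupuncture (pain, nausea, vomiting, palpitation, dizziness, headache, anorexia, and insomnia"). A dedicated record form is to be used, and each patient is to be asked about these events in the course of diagnosis and treatment. The same section says that all adverse events will be recorded, together with their causality.
- **Secondary outcomes.** One secondary outcome is the "gastrointestinal reaction score (postoperative pains, distention, nausea, vomiting"). Pain is rated three times a day. For the other two: "The extent of nausea is recorded using the VAS, postoperative from day 1 to 4", and "Vomiting will be counted daily".
- **Secondary outcomes, adverse events.** A second, shorter list appears here: "Adverse acupuncture events including subcutaneous hematoma, continuous acupuncture afterfeeling, and needle stagnation will be recorded by the assessor".
- **Acupuncture group.** "Acupuncture treatment will be performed once daily, consecutively over 4 days, starting on the first day after the laparoscopy".
- **Control group.** "Patients in CG will only receive ERAS care with no acupuncture intervention".
- **Background and rationale {6a}.** The condition under study is described as "accompanied by varying degrees of nausea, vomiting, and fever".

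**The concern.** The abstract names safety, alongside efficacy, as an aim of the trial. For symptoms that also occur without needling, a safety statement needs the rate in patients who were not needled. The trial has a randomised group of such patients, but the discomfort measure is tied to an event (a session) that this group never has.

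Two things are at stake. First, a rate from the acupuncture arm alone would be read as the discomfort rate of acupuncture when some or all of it is the aftermath of surgery. Second, if the form is completed only around sessions, the five discomforts outside the gastrointestinal score (palpitation, dizziness, headache, anorexia, insomnia) are solicited in one arm and left to spontaneous report or observation in the other. A difference could then appear without any effect of needling.

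**Working it through.** The plan states no rate, margin or power for this measure, so there is no figure to reproduce. The check compares the definitions and adds one illustration.

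**1. Timing.** Sessions fall on postoperative days 1 to 4. Nausea is scored on days 1 to 4. Vomiting is counted daily and pain is rated three times daily; no day range is printed for these two, but a daily schedule after surgery covers the session days.

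**2. Overlap of content.** Of the eight listed discomforts, three (pain, nausea, vomiting) are also components of the gastrointestinal reaction score. The other five are not.

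**3. Background.** Nausea and vomiting are symptoms of the condition by the protocol's own account. The Discussion also presents PC6 as a point used against postoperative nausea and LI4 as having analgesic properties. The trial therefore hopes to reduce symptoms that the harms section lists as discomfort when they follow a session.

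**4. Applicability to controls.** With neither needling nor sham, a discomfort after acupuncture is undefined in that arm.

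**5. Illustration (assumed rates, not from the documents).** Let p be the probability that a background symptom follows a session, and suppose acupuncture has no effect. Over 4 independent sessions the proportion of patients with at least one discomfort is 1 − (1 − p)^4, and the mean number per patient is 4p. With 80 patients in the arm:

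| p | 1 − (1 − p)^4 | patients of 80 | mean number, 4p |
|---|---|---|---|
| 0.05 | 0.185 | about 15 | 0.2 |
| 0.10 | 0.344 | about 28 | 0.4 |
| 0.20 | 0.590 | about 47 | 0.8 |
| 0.30 | 0.760 | about 61 | 1.2 |

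Independence matters for the incidence column. If the same patients have the symptom at every session, the incidence falls to p itself (5% to 30%). The mean 4p does not depend on independence.

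**6. Why the control rate is needed.** Suppose the background rate is 0.20 and acupuncture halves it to 0.10. The acupuncture arm then shows 34% with discomfort. Reported alone, that looks like harm; beside the 59% that the same checklist would give in controls, it is a benefit.

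**The case against.** A reader might infer more than the documents support, in four ways.

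- *That the safety result has no comparator.* The harms section records all adverse events without limit by arm and has each patient asked. The gastrointestinal score is not limited to the acupuncture arm, so pain, nausea and vomiting do have a concurrent control measurement. What stands is narrower: no comparison is defined for this list. The each-patient wording does not settle the matter, because the events it refers to include needle breakage and discomfort after acupuncture, which cannot be asked of a control.
- *That events are counted twice.* One vomiting episode can appear in both an efficacy score and a safety table, but these are two outcomes. No total combining them is planned, and reporting a symptom under both is not in itself an error.
- *That the two lists of acupuncture events contradict each other.* The list under Secondary outcomes is introduced by the word including, so it is not exhaustive. The lists differ and should be aligned, but this is a matter of harmonising wording.
- *That all eight discomforts are ordinary postoperative symptoms.* The protocol describes nausea and vomiting as symptoms of the condition and handles pain as a postoperative score. It says nothing of the kind about anorexia or insomnia.

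The strongest remaining objection is that causality is recorded, here and under Statistical methods {20a}, and that attribution rules may sit in the record form or the full protocol, which are not shown. The absence of such rules from an article is therefore no finding. However, case-by-case causality judgement, with patients and acupuncturists aware of allocation, is a weak substitute for a randomised comparison that is already available.

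**Conclusion.** The point holds as a limited, cheaply corrected weakness in how one safety measure is defined. As worded, the incidence and mean number of general discomforts after acupuncture describe the acupuncture arm only. They cannot separate harm from background, clearly so for nausea and vomiting and plausibly for the rest.

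The size is unknown from the documents. The range of 19% to 76% is an illustration that rests on assumed background rates of 5% to 30% per session, independent sessions and no acupuncture effect; it is not a forecast. Unequal ascertainment would follow if the form is used only around sessions, which the text suggests but does not state outright. The primary outcome is not affected.

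**What to change.** 1. Ask about the general discomforts with the same checklist, once daily on postoperative days 1 to 4, in both arms. Drop the reference to acupuncture from the question, and report the incidence and mean number by arm with the between-arm difference.
2. Take pain, nausea and vomiting from the scores already collected for the gastrointestinal reaction score, without collecting them again on the safety form.
3. Report needle-specific events (such as breakage, retained or stuck needle, fainting at needling, haematoma, local infection or abscess, persistent after-feeling) for the acupuncture arm only, from one list worded identically under Secondary outcomes and Adverse event reporting and harms {22}.

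The cost is revised wording in two sections and about five extra tick-boxes (palpitation, dizziness, headache, anorexia, insomnia) at a symptom assessment already made daily. The downside is a slightly longer daily form. Recruitment was under way when the article was written, so for patients already past day 4 the five added items may exist in the acupuncture arm only. The by-arm comparison of those items should then be limited to patients assessed after the change.
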